### Primary outcome measures

**Hypothesis 1:** Quality of dying of residents

The outcome measures to test hypotheses 1 include several aspects of quality of dying of the residents of the participating long-term care facilities (LTCFs).

- End-of-Life in Dementia – Comfort Assessment in Dying (EOLD – CAD)
  - Comfort during the last 7 days of life
  - Answered by the staff most involved in care and the most closely involved relative of the deceased resident at baseline, month 13 (T1), and 17 (T2)
- Quality of Dying in Long-Term Care (QOD – LTC):
  - Quality of dying in long-term care
  - Answered by the staff most involved in care for the deceased resident at baseline, month 13 (T1) and 17 (T2)

**Hypothesis 2:** Staff attitudes and knowledge towards palliative care

The outcome measures to test hypotheses 2 include several aspects of the attitudes and knowledge towards palliative care of staff in the participating LTCFs. These outcome measures were answered by all care staff present in participating LTCFs during data collection at baseline and month 12.

- End-of-Life Professional Caregiver Survey (ECPS)
  - Staff attitudes towards patient and family communication, cultural, and ethical values
- Palliative Care Survey (PCS)
  - Staff knowledge on palliative care
- Self-Efficacy in End-of-Life Care Survey (S-EOLC)
  - Staff confidence in communicating with residents and families about end-of-life (i.e. self-efficacy)

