**Sample**

**Hypothesis 1:** To test hypotheses 1, all deceased residents for whom the staff most involved in care for the deceased resident completed a questionnaire will be included in the sample.

**Hypothesis 2:** To test hypotheses 2, all care staff present in participating LTCFs during data collection, who completed a questionnaire regarding their attitudes and knowledge towards palliative care, will be included in the sample.

**Hypothesis 3:** To test hypotheses 3, all deceased residents for whom the most closely involved relative of the deceased resident completed a questionnaire will be included in the sample.

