## **Data analyses**

### **Step 1.** Exploring the data and data assumptions

The nature of each variable, as well as the influence of certain data assumptions on the study results must be explored prior to primary data analyses.

**Step 1.1.** Explore the number of cases in T1 and T2 to determine statistical power for each post intervention measurements. T1 and T2 can be used separately for the analysis when statistical power is at least 80%.

**Step 1.2.** Due to potential turn-over of staffs in LTCFs, the samples – care staffs present in participating LTCFs during data collection– with both the baseline and post-intervention measurements will be explored.

**Step 1.3.** Check data assumptions for regression analyses.

**Normality of distribution** – For continuous variables, a graphical representation (histogram) or the Shapiro Wilk-test or Kolmogorov Smirnov test can be used to check for normality of the distribution. If the normality of distribution is violated, log-transformation may for example be done. The partner responsible for conducting the analysis would need to discuss in the consortium on how skewed data can further be used for the analysis.

**Linearity** – Linearity between the outcome measures and the intervention variable or covariates will be checked through visual inspection of the scatter diagram. If the assumption of linearity is violated, the partner responsible for conducting the analysis would need to discuss in the consortium on how these data can be further used for the analysis – e.g. transforming into quartiles.

**Step 1.4.** Prepare the variables to be used for the data analyses based on the exploration of data and data assumptions.

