### ***Regression analyses***

To test the study hypotheses, several regression analyses will be conducted based on the exploration of data and data assumptions, as well as on the data analysis approach to be used (ITT and per protocol). Generally, all primary and secondary outcome measures (scale sum scores) are by nature continuous variables, which would require multivariate linear regression analysis techniques. However, if the assumptions of normal distribution and/or linearity is/are violated, multivariate logistic (or ordinal) regression analyses may be applicable. The specific procedure on how to further analyse skewed or non-linear data will rely upon the decision of the consortium. Basically, multivariate linear or logistic regression analyses may be performed to assess and compare the baseline and post-intervention measurement differences in the outcome measures between the intervention group and the control group, while adjusting for sample characteristics that may differ between groups.

Additionally, multi-level mixed model regression analyses will be performed to account for the baseline measurement and the multilevel nature of the data – e.g. residents and staff nested within LTCFs or country. The kind of multilevel mixed model regression analyses will depend on the nature of the outcome variables and the statistical package to be used for the main analyses.

With the multi-level mixed model analyses, outcomes will be analysed with LTCFs and country as random factor, and group, time point, and their interaction as fixed factors. Differences in mean change (post-intervention measurements minus baseline) between the intervention group and the control group (interaction group\*time) will be calculated. Estimated means with corresponding 95% CI will be reported at baseline and follow-up, both for the intervention and control group. Moreover, estimated differences (and 95%CI) in change between intervention and control are reported. The effect sizes (Cohen's *d*) using the baseline-adjusted mean differences and the variance between residents or care staffs, between LTCFs, and between country will be estimated to assess the magnitude of the effects for the different outcome measures.

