All analyses will be two-tailed and considered significant if  $\alpha = 0.05$ . In addition, data will be analysed by using statistical software program suitable for the necessary statistical analyses, such as multilevel mixed model analysis and multiple imputation – e.g. STATA, SAS, or IBM SPSS.

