### **5. Evaluation questionnaire after 6th training session**

#### ***RE-AIM elements: Implementation, Maintenance***

After the last training session (step 6), all care staff members received a written evaluation questionnaire. The evaluation questionnaire is linked to the same staff member as in the baseline measurement (T0), by using the same list linking the anonymous code to the listed staff member (kept in the LTCF). In this way, it can be investigated whether the number of sessions that an individual care staff member reported to have attended is associated with the differences found between measurements T0 and T1. Information from the evaluation questionnaires will be entered in a database (LimeSurvey).

The evaluation questionnaires contain information on the following variables:

- Characteristics of participants (age, gender, function, number of hours per week working in LTCF)

- Satisfaction with trainer (regarding 4 aspects – expertise, conveying theory and skills, giving room for questions and discussions, overall teaching competences)
- Evaluation of number and length of training sessions
- Which training sessions were attended
- Evaluation of how much was learned from each training session
- Evaluation of how difficult or easy it was to fill in PACE documents
- Evaluation of usefulness of PACE documents
- Intention to use PACE documents in the future
- Overall evaluation of complete PACE Program
- Confidence towards PACE Program supporting staff to provide good palliative care
- Whether or not the PACE Program would be recommended to other LTCFs

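### The mixed model listed for the staff outcomes (Hypothesis 2) has no staff-level term, so a returning staff member's two scores are treated as independent

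*Combined protocol and SAP*

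**What the plan says.** Hypothesis 2 is one of two primary hypotheses. Its three scales were "answered by all care staff present in participating LTCFs during data collection at baseline and month 12" (Primary outcome measures). The analysis sample is "all care staff present in participating LTCFs during data collection, who completed a questionnaire regarding their attitudes and knowledge towards palliative care" (Sample), so a questionnaire at both waves is not required.

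Two places bear on pairing:

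- Step 1.2 expects turnover and says that staff "with both the baseline and post-intervention measurements will be explored". It does not say what follows from this.
- The process evaluation plan, item 5 (evaluation questionnaire after the sixth training session), says that this questionnaire is "linked to the same staff member as in the baseline measurement (T0), by using the same list linking the anonymous code". The stated purpose is to relate the number of sessions a person attended to the T0-T1 differences, which presupposes that T0 and T1 can be matched per person.

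The model, in Regression analyses, is the same for staff and for deceased residents: "outcomes will be analysed with LTCFs and country as random factor, and group, time point, and their interaction as fixed factors". It names no staff random effect, no within-person covariance and no own-baseline covariate. The section also says that the model is meant to take the baseline into account, mentions staff-level variance when describing Cohen's *d*, and leaves the kind of mixed model to depend on the outcome type and the software.

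**The concern.** Hypotheses 1 and 3 concern different deceased residents at each wave, so LTCF and country are natural levels there. Hypothesis 2 differs because a staff member who stays contributes two scores, and two scores from one person on an attitude or knowledge scale would normally be positively correlated. With the listed terms, those two scores are independent once LTCF and country are given.

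The group*time contrast is a difference in change. Positive covariance between a person's two scores lowers its true variance, and a model that ignores the covariance reports a standard error that is too large for that reason. A real programme effect on staff knowledge or attitudes could then be missed on a primary hypothesis. Nothing here biases the estimate.

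**Working it through.** **Inputs from the documents.** Two-sided testing at 0.05 ("All analyses will be two-tailed and considered significant if" α = 0.05). The only power figure is a rule for the two post-intervention waves: "T1 and T2 can be used separately for the analysis when statistical power is at least 80" per cent. It is not a design figure for Hypothesis 2. No staff numbers, effect size, ICC, overlap or within-person correlation are given, so there is no figure to reproduce.

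**Assumptions.** Total variance 1 and equal arms; m = 10-20 staff per LTCF per wave; ICC = 0.05-0.10; cluster autocorrelation CAC = 0.8-1; share of staff measured twice π = 0.5-1; within-LTCF correlation of a person's two scores ρ = 0.5 or 0.3. Variance components are held at these values.

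**Formulas, difference in change.** Let A = 2·ICC·(1−CAC) and B = 2(1−ICC)/m. Per LTCF, and up to a constant that cancels:

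- variance the unlinked model reports: V_rep = A + B
- true variance of its estimate: V_true = A + B(1−πρ)
- variance with the link, unpaired staff kept: V_link = A + B/[π/(1−ρ) + 1−π]

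Set the effect so that the unlinked model has nominal 80% power (2.80 reported standard errors). Actual power is then Φ(0.84·√(V_rep/V_true)) without the link and Φ(2.80·√(V_rep/V_link) − 1.96) with it.

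**Example.** m = 20, ICC 0.05, CAC 0.8, π = 0.7, ρ = 0.5. A = 0.02 and B = 0.095.

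- V_rep = 0.115
- V_true = 0.02 + 0.095×0.65 = 0.0818
- V_link = 0.02 + 0.095/1.7 = 0.0759

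The link lowers the true variance by 1 − 0.0759/0.0818 = 7%. Actual power goes from 84% to 93%. If the two arms are given a common baseline mean instead, the same inputs give a 10% cut and a rise from 82% to 90%.

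**Range over the assumed grid**

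| | ρ = 0.5 | ρ = 0.3 |
|---|---|---|
| Gain in actual power (both forms) | about 6-11 points | about 3-8 points |
| Cut in true variance, difference in change | 0-11% | 0-3% |
| Cut in true variance, common baseline mean | 5-16% | 2-5% |
| Actual power without the link | 81-88% | 81-84% |

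At complete pairing the difference-in-change estimate is the same with or without the link (1−πρ and 1/[π/(1−ρ)+1−π] both equal 1−ρ when π = 1). There the whole gain is in the reported standard error. At 20% overlap and ρ = 0.3 the gain is only about 1-2 points, and with no overlap it is zero.

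**The model exactly as listed.** It has no LTCF-by-time term either. Its ratio of true to reported variance is (1−πρ) + m·ICC·(1−CAC)/(1−ICC). With ICC 0.05 and m = 20:

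| (π, ρ) | CAC = 1 | CAC = 0.8 |
|---|---|---|
| (0.3, 0.3) | 0.91 | 1.12 |
| (0.5, 0.5) | 0.75 | 0.96 |
| (0.7, 0.7) | 0.51 | 0.72 |

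Without LTCF-by-time variance the test is conservative (actual two-sided error about 0.040, 0.024 and 0.006). With it, the two omissions pull in opposite directions.

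**The case against.** The strongest reply is that the plan is less closed than it looks. Baseline scores do enter, the kind of model is left open, staff-level variance is mentioned, and Step 1.2 looks at paired staff before variables are prepared. Part of this stands: a reader might infer that the baseline is ignored, and the documents do not support that. The rest does not settle the matter. The model choice is tied to outcome type and software, not to repeated measurement of staff. The staff-variance wording also covers residents, who have one record each, so it can simply mean residual variance.

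Linkage is also weaker than a reader might infer. The code list is described for the post-training questionnaire, which concerns intervention facilities. Linkage from baseline to follow-up is implied by the planned T0-T1 comparison, and in the control arm at most by Step 1.2. Joiners have no baseline and leavers no follow-up. This stands.

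A reader might also compare V_link with V_rep and infer that the link cuts the variance by 23-50% at ρ = 0.5. That compares a true variance with a misreported one. Against the true variance of the unlinked estimate the cut is 0-16% across both forms. Likewise, a real error rate near 0.6% at ρ = 0.5 needs complete pairing and no LTCF-by-time variance. Step 1.2 expects turnover, which speaks against complete pairing.

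One further limit stands. If an LTCF-by-time variance is estimated freely without a staff term, it can absorb part of the missing covariance. With m = 20, ICC 0.10, CAC 0.8, π = ρ = 0.5, the true component is 0.10×0.2 = 0.02, and the missing covariance is 0.9×0.5×0.5/20 = 0.011. The fitted component would fall to about 0.009 and the standard error would be about right. The gain is then only the 7% cut in true variance (0.1075 to 0.1000).

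**Conclusion.** The point holds as an efficiency and specification defect in a primary analysis. The listed Hypothesis 2 model leaves the within-person link unused. With positive within-person correlation and LTCF-by-time variance held at its true value, its standard error for group*time is too large and the test conservative. The likely gain from repair is about 6-11 points of actual power at ρ = 0.5 and 3-8 at ρ = 0.3, mostly through a correct standard error.

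These sizes rest wholly on the assumed grid. They shrink with low overlap, or where a fitted LTCF-by-time component absorbs the covariance. They also require that codes link both arms. With LTCF-by-time variance omitted as well, as in the listed terms, the net error in the standard error can have either sign, so the documents do not support calling the planned test conservative without that condition. The point does not extend to Hypotheses 1 and 3.

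**What to change.** In Regression analyses, state a separate Hypothesis 2 mixed model:

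- all baseline and follow-up staff records in one model;
- a staff random effect (or a T0-to-follow-up covariance by staff code) nested in LTCF;
- LTCF, LTCF-by-time and country effects;
- staff seen at only one wave kept, so the stated sample is unchanged.

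Confirm that the codes link baseline to follow-up in both arms, and report the number of staff linked per arm. Codes that cannot be matched are analysed as unpaired.

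A regression of the follow-up score on the person's own baseline with a missing-baseline indicator should not be offered as equivalent. It conditions on having joined after baseline, which the programme could affect, and it drops leavers' individual baseline records.

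The follow-up wave also needs one label: Primary outcome measures places it at month 12, while the process evaluation plan (Table 1 and item 7) places the T1 staff questionnaire at month 13.

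The cost is SAP wording, a file merge by code and one extra covariance parameter for the within-person link. If the control-arm codes turn out not to link, the gain there is not available.

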### ***Regression analyses***

For this sub-analysis, several regression analyses will be conducted based on the exploration of data and data assumptions, as well as on the data analysis approach to be used (ITT and per protocol). Generally, the EOLD-CAD or QOD-LTC variables are by nature continuous variables, which would require multivariate linear regression analysis techniques. However, if the assumptions of normal distribution and/or linearity is/are violated, multivariate logistic regression analyses may be applicable. The specific procedure on how to further analyse skewed or non-linear data will rely upon the decision of the consortium. Basically, multivariate linear or logistic regression analyses may be performed to assess and compare the baseline and post-intervention measurement differences in the quality of dying between residents with and without dementia, both for the intervention group and the control group, while adjusting for sample characteristics that may differ between groups.

Additionally, multi-level mixed model regression analyses will be performed to account for the baseline measurement and the multilevel nature of the data – e.g. residents and staff nested within LTCFs or country. The kind of multilevel mixed model regression analyses will depend on the nature of the outcome variables and the statistical package to be used for the main analyses.

With the multi-level mixed model analyses, the outcomes will be analysed with LTCFs and country as random factor, and group, time point, and their interaction as fixed factors. Differences in mean change (post-intervention measurements minus baseline) between deceased residents with and without dementia, both for the intervention group and the control group (interaction group\*time\*dementia) will be calculated. Estimated means with corresponding 95% CI will be reported at baseline and follow-up, both for the intervention and control group. Moreover, estimated differences (and 95%CI) in change between intervention and control will be reported. The effect sizes (Cohen's *d*) using the baseline-adjusted mean differences and the variance between residents or care staffs, between LTCFs, and between country will be estimated to assess the magnitude of the effects for the different outcome measures.

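### The mixed model names no LTCF-by-time or staff-member random effect, so the group*time interval is too narrow for resident and relative outcomes if LTCF means drift differently, and miscalibrated in an uncertain direction for staff outcomes.

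*Combined protocol and SAP*

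**What the plan says.** Under Regression analyses in Step 4 of the outcome evaluation plan, "outcomes will be analysed with LTCFs and country as random factor, and group, time point, and their interaction as fixed factors". The effect of interest is the group*time interaction: "Differences in mean change (post-intervention measurements minus baseline) between the intervention group and the control group". For the effect sizes, "the variance between residents or care staffs, between LTCFs, and between country will be estimated"; that list has no LTCF-by-time component. The model type is left partly open: "The kind of multilevel mixed model regression analyses will depend on the nature of the outcome variables and the statistical package".

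The Regression analyses text for the dementia sub-group example repeats the structure: "the outcomes will be analysed with LTCFs and country as random factor, and group, time point, and their interaction as fixed factors".

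On significance, "All analyses will be two-tailed and considered significant if" alpha is 0.05. The only statement on power is a rule for the follow-up waves: "T1 and T2 can be used separately for the analysis when statistical power is at least 80" percent. No number of LTCFs, cluster size or ICC is given.

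Three other places matter here:
- Primary and Secondary outcome measures, with Data collection in the cost-effectiveness plan, show that residents are assessed after death at baseline, month 13 and month 17. Each wave therefore holds different residents. Staff are surveyed at baseline and month 12, taking everyone present, so some answer twice. Step 1.2 expects turnover and plans to explore staff with both measurements.
- The process evaluation plan, item 5, links the post-training questionnaire to the baseline staff member "by using the same list linking the anonymous code to the listed staff member".
- Cluster-robust standard errors are specified in the cost-effectiveness plan, for the net-benefit regressions, and not for the outcome models.

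**The concern.** With a random LTCF intercept alone, two residents of one LTCF are equally correlated whether they died in the same wave or a year apart. The LTCF effect then drops out of the before-after difference, and only respondent-level noise enters the standard error of group*time. If LTCF means also move differently over a year, for example through the turnover that Step 1.2 expects among the staff who rate the Hypothesis 1 outcomes, that movement is part of the true error and is not counted. The standard error is then too small.

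For Hypothesis 2 there is a second omission. Staff who answer at both waves are positively correlated with themselves, which makes their change more precise than the model assumes. Leaving out a staff-member effect makes the standard error too large.

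The group*time contrast is the plan's measure of effect for every primary and secondary outcome, so its confidence intervals and p-values are at stake.

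**Working it through.** **Reproducing the stated level.** For a two-sided test at 1.96, 2 × (1 − Φ(1.96)) = 0.050. The written model attains this when LTCF-by-time variance is zero and different people are measured at each wave. There is no sample size or power figure to reproduce.

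**Inputs.** The random factors, the contrast and alpha come from the plan. All of the following are assumptions: ICC ρ from 0.02 to 0.10; m = 5 to 20 respondents per LTCF per wave; correlation r of an LTCF's effect across waves from 0.5 to 1 (1 means no drift); two balanced waves; total variance 1.

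**Resident and relative outcomes.** Let se² = 1 − ρ (respondent variance) and sct = ρ(1 − r) (LTCF-by-time variance).
- The true variance of group*time is proportional to se²/m + sct.
- The written model uses s²/m, with s² = [(2m − 2)se² + (se² + m·sct)]/(2m − 1).
- The variance is understated by the factor R = (se² + m·sct)/s².
- Type I error = 2Φ(−1.96/√R).

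Example with ρ = 0.05, r = 0.8, m = 20:
- sct = 0.05 × 0.2 = 0.01, and se² + m·sct = 0.95 + 0.20 = 1.15.
- s² = (38 × 0.95 + 1.15)/39 = 0.955.
- R = 1.204, so the standard error is 91% of its correct value and the type I error is 7.4%.

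With m = 10 instead, R = 1.05/0.955 = 1.099, the standard error is 95% of its correct value and the type I error is 6.2%.

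Over ρ = 0.02 to 0.10 and m = 5 to 20:

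| Across-wave correlation r | Type I error |
|---|---|
| 1.0 (no drift) | 5.0% |
| 0.9 | 5.1% to 7.5% |
| 0.8 | 5.2% to 10.1% |
| 0.5 | 5.5% to 17.1% |

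A simulation of 4,000 trials per scenario agrees. With ρ = 0.10, r = 0.8 and m = 20 it gave 10.4% with either 20 or 40 LTCFs per arm, against 10.1% by formula.

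**Staff outcomes.** Suppose a fraction f of staff answers twice, with within-person residual correlation p.
- The true variance becomes proportional to (se²/m)(1 − f·p) + sct.
- The model's s² becomes 2m(se² + sct − v)/(2m − 1), with v = se²(1 + f·p)/(2m) + sct/2.

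Example with ρ = 0.05, r = 0.8, m = 20, f = p = 0.5:
- True term: 0.0475 × 0.75 + 0.01 = 0.0456.
- v = 0.02375 × 1.25 + 0.005 = 0.0347, so s² = 40 × (0.96 − 0.0347)/39 = 0.949.
- Model term: 0.949/20 = 0.0475.
- The ratio is 0.96 and the type I error is 4.6%.

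Type I error with ρ = 0.05, m = 20, p = 0.5:

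| Staff answering twice | r = 1.0 | r = 0.8 | r = 0.5 |
|---|---|---|---|
| 0% | 5.0% | 7.4% | 11.0% |
| 50% | 2.4% | 4.6% | 8.2% |
| 70% | 1.6% | 3.5% | 7.0% |

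**After the change.** In the simulation without repeated respondents, group*time was tested against LTCF-by-time variation on a t distribution. The type I error was 4.1% to 6.0% in every scenario, with Monte Carlo error of about 0.35 points. Repeated staff were not simulated.

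**The case against.** The strongest objection is that the harm depends on a quantity the documents do not give. With no differential drift the resident test has its nominal level, and with small clusters and mild drift the excess is slight: ρ = 0.05, r = 0.9 and m = 5 gives 5.3%. This stands. A reader might infer that the false-positive rate exceeds 5% as a matter of fact, but the documents support only the conditional statement.

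A reader might also infer much larger errors. With 30 respondents per LTCF per wave and ρ = 0.10, the formula gives 12.7% at r = 0.8 and 19.4% at r = 0.6. Nothing in the documents supports 30 completed questionnaires on deceased residents per LTCF per wave. For staff, the 12.7% assumes that nobody answers twice; with 50% overlap and p = 0.5 it falls to 9.8%. Three of the five primary instruments are staff outcomes, and for them the test can be conservative. A general claim that it is anti-conservative is not supported.

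The wording is also less than an explicit restriction. It speaks of random factors, leaves the kind of mixed model open, and Step 1.2 already looks at staff with both measurements. That is fair, but the listed variance components make random intercepts the natural reading. None of this text supplies the missing terms, and choosing them after seeing the data would be a risk in itself.

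Finally, the coding list is described for the post-training questionnaire. Linkage from baseline to follow-up in control LTCFs is not expressly stated, so a staff-member effect is feasible only if that linkage exists.

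**Conclusion.** The concern holds in conditional form. For resident and relative outcomes, the written model gives a group*time standard error that is too small whenever LTCF means drift differently over time. The type I error is about 5% to 10% for an ICC of 0.02 to 0.10, 5 to 20 respondents per LTCF per wave and an across-wave correlation of 0.8 to 0.9. It is higher with stronger drift and 5% with none. All of these inputs are assumptions.

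For staff outcomes the interval is generally miscalibrated and the direction is uncertain. With 50% to 70% of staff answering twice and p = 0.5, the scenarios run from about 1.6% to 9.8%.

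In the sub-group example the calculation applies to the difference in change between arms. It does not carry over to the three-way interaction with dementia, because drift shared by both dementia groups would largely cancel there.

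**What to change.** In both Regression analyses sections (Step 4 and the sub-group example), add a random LTCF-by-time-point effect to the LTCF and country effects for all outcomes, and test group*time with Satterthwaite or Kenward-Roger degrees of freedom. For Hypothesis 2 also add a staff-member random intercept where the anonymous codes link baseline to follow-up in both arms, and state whether control LTCFs kept that link. Fix this before analysis, so that the random structure is not chosen from the results.

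The cost is a few sentences and two more variance components to estimate. Intervals for resident and relative outcomes become somewhat wider if drift is present. If it is absent, the added variance is estimated near zero and little is lost. The LTCF-by-time term needs no new data.

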#### DATA COLLECTION

Data were collected within the PACE Study II project. Retrospective data collection of deceased residents took place at the start of the trial (month 1) and at month 13 and 17 of the trial.

PACE staff questionnaires regarding care services received during the *last month of life* are used to determine resource use by residents from. Direct medical resource use was collected on a per patient basis in the participating facilities, using (parts of) the resource use in dementia (RUD). Direct medical costs include care received in the last months of life, such as hospital admission, care received in an emergency room, treatments in the last month of life, adverse events in the last month of life, or opioids, antipsychotics, hypnotics or sedatives. Additionally, data on PACE-related costs are also collected.

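### For the outcomes measured on deceased residents, the unconstrained difference in change is unbiased but less precise than a model with a common or adjusted baseline

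*Combined protocol and SAP*

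**What the plan says.** Step 4 of the outcome evaluation plan (Regression analyses) brings in the multilevel model as follows: "Additionally, multi-level mixed model regression analyses will be performed to account for the baseline measurement and the multilevel nature of the data". It then gives the structure: "outcomes will be analysed with LTCFs and country as random factor, and group, time point, and their interaction as fixed factors". The reported effect is the group-by-time interaction: "Differences in mean change (post-intervention measurements minus baseline) between the intervention group and the control group". The baseline difference between arms is therefore a free parameter.

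No model with a common baseline mean, or with the facility's baseline mean as a covariate, is described. The nearest wording concerns Cohen's d only, which is to be computed "using the baseline-adjusted mean differences and the variance between residents or care staffs, between LTCFs, and between country". The same section also lists multivariable linear or logistic regressions and does not say which model is primary.

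On sampling, the cost-effectiveness plan (Data collection) says: "Retrospective data collection of deceased residents took place at the start of the trial (month 1) and at month 13 and 17". The three waves of deaths are thus repeated cross-sections of different residents in the same facilities. Step 4 says that the groups were randomised.

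Power appears only as a rule in Step 1.1: "T1 and T2 can be used separately for the analysis when statistical power is at least 80" per cent. The documents give no number of facilities, deaths per facility, ICC, SD or effect size.

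**The concern.** No resident is measured twice, so for these outcomes the only link between baseline and follow-up is the facility. A facility mean based on a few deaths is mostly sampling noise, and noise in the baseline mean says little about the follow-up mean. A plain difference in change gives the baseline mean a weight of one, whatever its predictive value. Randomisation allows that weight to be estimated instead, because the arms share the same expected baseline.

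What is at stake is precision for hypotheses 1 and 3, from data that the trial already holds. Step 1.1 makes the separate use of T1 and T2 depend on 80% power, so a noisier estimator than necessary can also affect that decision.

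**Working it through.** The plan has no computed figure to reproduce; the 80% in Step 1.1 is only a threshold.

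**Inputs.** From the documents: randomised groups, different deceased residents at months 1, 13 and 17, two-sided alpha 0.05. Assumed, because the documents are silent: m = deaths per facility per wave, ICC, and k = correlation of a facility's true effect between waves. Main range: m 5 to 10, ICC 0.05 to 0.10, k 0.6 to 1.0.

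**Formulas.** Set the total variance to 1.

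- Variance of a facility mean: V = ICC + (1 - ICC)/m. Covariance between waves: C = ICC × k. Correlation of facility means: r = C/V.
- Per-facility variance relative to using follow-up only, equal waves: difference in change 2(1 - r); common baseline or baseline-adjusted 1 - r².
- Variance ratio, change over common baseline: 2(1 - r)/(1 - r²) = 2/(1 + r). This exceeds 1 for every r below 1.
- Standard error of the common-baseline estimate relative to change: √[(1 + r)/2].

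**Results.**

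| ICC | k | m | r | Change / follow-up only | Common baseline / follow-up only | Change / common baseline | SE relative to change |
|---|---|---|---|---|---|---|---|
| 0.05 | 0.6 | 5 | 0.03/0.24 = 0.125 | 1.75 | 0.98 | 1.78 | 0.75 |
| 0.05 | 0.8 | 10 | 0.04/0.145 = 0.28 | 1.45 | 0.92 | 1.57 | 0.80 |
| 0.10 | 0.8 | 10 | 0.08/0.19 = 0.42 | 1.16 | 0.82 | 1.41 | 0.84 |
| 0.10 | 1.0 | 10 | 0.10/0.19 = 0.53 | 0.95 | 0.72 | 1.31 | 0.87 |
| 0.10 | 0.8 | 20 | 0.08/0.145 = 0.55 | 0.90 | 0.70 | 1.29 | 0.88 |
| 0.20 | 1.0 | 5 | 0.20/0.36 = 0.56 | 0.89 | 0.69 | 1.29 | 0.88 |

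The first and fourth rows are the extremes of the main range; the last two lie outside it.

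**Power, as illustration.** If the change contrast had 80% power, the other model would have Φ(2.80/SE ratio - 1.96): Φ(1.77) = 96% at 0.75 and Φ(1.25) = 89% at 0.87.

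**Unequal facility sizes.** Generalised least squares with 80 facilities (assumed), k = 0.8 and a mean of 10 deaths, scaled so that follow-up only has 80% power: change 63% against common baseline 83% at ICC 0.05; 73% against 87% at ICC 0.10.

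**Wider range.** Over ICC 0.02 to 0.20, k 0.6 to 1.0 and m 3 to 30, change over common baseline is 1.06 to 1.93. With T1 and T2 pooled (follow-up twice the size of baseline; ICC 0.05 to 0.20, k 0.8 and 1.0, m 5 to 20) it is 1.13 to 2.20.

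**Against ignoring baseline.** Change is noisier than follow-up only when V exceeds 2C at baseline, that is, when baseline deaths per facility are below (1 - ICC)/[ICC(2k - 1)]. At k = 1.0 this is 19, 9 and 4 for ICC 0.05, 0.10 and 0.20; at k = 0.8 it is 31.7, 15 and 6.7. On a grid of five ICCs (0.02, 0.05, 0.10, 0.15, 0.20) and three k (0.6, 0.8, 1.0), change is noisier in 51 of 60 settings with m of 3, 5, 8 or 10. With m of 15, 20 or 30 it is noisier in 22 of 45, with two exact ties: 0.9/(0.1 × 0.6) = 15 and 0.8/(0.2 × 0.2) = 20.

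**Cost if the baselines are not comparable.** The common-baseline estimate subtracts r times the baseline difference; the change estimate subtracts all of it. Suppose knowledge of allocation shifts ratings in one arm by d. If the shift is the same in both waves, change removes it and the common-baseline model keeps (1 - r)d, which is 0.47d to 0.88d over the main range. If the shift is at baseline only, change is off by d and the common-baseline model by rd.

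**The case against.** The strongest objection concerns the condition. The common-baseline model needs equal expected baseline scores as recorded, not only equal underlying care. Ratings come from facility staff and relatives, only completed questionnaires count, and the documents do not say whether the month 1 collection came before allocation or whether raters knew it. If a rating or response difference existed and persisted, the planned contrast would remove it and the alternative would not. This stands, and the recommendation is conditional on it.

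Second, the hypotheses are worded as a comparison with usual care relative to baseline, and a difference in change estimates that directly and without bias. True, but under randomisation the common-baseline effect targets the same quantity, so the choice is one of efficiency. A reader might infer that the planned estimate is biased; nothing in the documents supports that.

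Third, a reader might infer that the change contrast is usually worse than ignoring baseline altogether. The documents give none of the inputs needed, and the ratio over the main range, 0.95 to 1.75, crosses 1. It can be worse with few baseline deaths and a low ICC; it reverses with more deaths or a higher ICC.

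Fourth, a reader might extend the argument to the staff outcomes. Step 1.2 and the process evaluation (item 5, evaluation questionnaire) show that some staff have linked repeat measurements, so calculations for separate cross-sections do not describe them.

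Finally, the section leaves the primary model and the kind of multilevel model open. That is so, but the only effect it defines from the multilevel model is the unconstrained interaction.

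**Conclusion.** The point holds for EOLD-CAD, QOD-LTC and EOLD-SWC as a loss of precision, not as a threat to validity. That the unconstrained contrast is less precise needs only randomisation, baseline scores unaffected by allocation, r below 1, and a baseline weighted by its actual predictive value. The size rests on assumed inputs: over the main range the standard error of the alternative is about 75-87% of the change-score standard error, with equal wave sizes. The gain shrinks as r approaches 1. No conclusion is drawn for the staff outcomes, or about change scores against ignoring baseline in general.

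**What to change.** In Step 4, Regression analyses, for the three outcomes on deceased residents:

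- Make the primary effect the post-intervention difference between arms from a mixed model with a common baseline mean (fixed effects: time and group-by-post, no group effect at baseline), or from a model adjusted for the facility's baseline mean.
- State the condition, and have the sponsor confirm it: baseline ratings and response were obtained before, or without knowledge of, allocation.
- Keep the unconstrained group-by-time difference in change as a sensitivity analysis, and as primary if the condition cannot be confirmed.
- Report observed baseline means by arm descriptively, since a common-baseline model does not yield the separate estimated baseline means that the section now promises.
- Bring the dementia example under Sub-group data analysis, which repeats the same structure, into line.

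The cost is a revision of the SAP text, with the same data and software. The downside is reliance on the equal-baseline condition.
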